## Interventions

### Explanation for the choice of comparators {6b}

In Phase Ib, no comparator will be used as the primary objective is to determine the maximum tolerated dose (MDT) in gastric tumors and acute leukemias. In Phase II, a placebo group will be included for gastric tumors, while both groups will receive the standard chemotherapy for their respective underlying diseases. However, for acute leukemias, a comparison will be made with a cohort of historical records from the hospital where the relevant clinical outcomes have already been established, considering the causal factors.

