### Participant timeline {13}

#### Sample size {14}

For phase I, a sample size of 6 patients was determined for gastric tumors and acute leukemias. In case of presentation of any adverse event in the first in these patients, the dose will be decreased for the second cycle; in case of an adequate safety profile, the dose will be doubled for the second cycle.

The sample sizes for phase II were determined for both gastrointestinal tumors and hematologic tumors. For gastrointestinal tumors, a sample size of 30 patients was calculated, with 15 patients per group, considering a mean difference of at least 6 points in quality of life, a standard deviation of 5 and 6 points for each group, an alpha error of 0.05, and a beta error of 0.20. Additionally, a 10% allowance was added for possible study losses. For hematologic tumors, the sample size calculation was based on response criteria such as improvement, remission rate, and hematologic recovery. The ANOVA test was used, an alpha error of 0.05, a beta error of 0.20, and an effect size of 0.4. The resulting sample size was 28.

It should be noted that these sample sizes will be reassessed at the end of phase I for both gastric tumors and acute leukemia. The recalculated sample size for phase I/II is 36 for gastrointestinal tumors and 46 for hematologic tumors.

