### Interim analyses {21b}

At the end of phase I, an analysis of the safety profile will be conducted to evaluate the adverse events and determine if any additional safety tests or measures need to be implemented in phase II. This analysis will provide valuable insights into the safety and tolerability of the intervention.

Based on the initial results from phase I, the sample size for phase II will be recalculated, taking into consideration the outcomes observed during phase I. This recalculation aims to ensure an appropriate sample size that allows for robust statistical analysis and meaningful conclusions in phase II.

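### Phase II is to be resized from a six-patient, uncontrolled phase I that schedules no efficacy measure, and totals are already labelled as recalculated before phase I has begun

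*Protocol article*

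**What the plan says.** Sample size {14} gives the phase I number: "For phase I, a sample size of 6 patients was determined for gastric tumors and acute leukemias". For the gastrointestinal part of phase II, "a sample size of 30 patients was calculated, with 15 patients per group". The inputs to that figure are a target difference of 6 points on the quality-of-life scale, SDs of 5 and 6, alpha 0.05, beta 0.20 and a 10% allowance for losses. The leukaemia figure is 28.

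The section then says that "these sample sizes will be reassessed at the end of phase I for both gastric tumors and acute leukemia". Interim analyses {21b} repeats the commitment: "the sample size for phase II will be recalculated, taking into consideration the outcomes observed during phase I". The stated aim there is an adequate size for a sound analysis. Neither section names the quantity to be updated.

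The sentence after the commitment in Sample size {14} reads: "The recalculated sample size for phase I/II is 36 for gastrointestinal tumors and 46 for hematologic tumors". Recruitment {15} and Trial status both put the start of recruitment in the future.

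On what phase I can deliver, Explanation for the choice of comparators {6b} says: "In Phase Ib, no comparator will be used as the primary objective is to determine the maximum tolerated dose". Intervention description {11a} moves the same patients to a different dose after four weeks. Table 1, the phase I schedule, lists visits, dispensing and safety tests. It has no QLQ-C30, RECIST, myelogram or flow cytometry, all of which appear in the phase II schedules (Tables 2 and 3).

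**The concern.** A resizing step needs an estimate of something in the sample size formula: a treatment difference, an SD or a response rate. Phase I has no control group, so it gives no treatment difference. Its schedule collects neither the gastrointestinal primary outcome nor leukaemia response. Even if those were added, six patients observed across two dose levels would give a very imprecise value. The gastrointestinal comparison is the only randomised one in the trial. If its size were cut because six patients happened to have similar scores, it could no longer detect its own 6-point target, and a negative result would say little.

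The printed totals add a second difficulty. The size is described as already recalculated and as still to be recalculated, so a reader cannot tell which number governs.

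**Working it through.** **Inputs.** From Sample size {14}: difference 6, SDs 5 and 6, alpha 0.05, power 80%, 10% losses, 15 per group, six phase I patients. Assumed: a two-sided test (sidedness is not stated); six patients per tumour type (36 = 30 + 6 supports this for the gastrointestinal group); an update of the SD only, by the normal formula, with no floor; normally distributed scores.

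**Step 1: reproduce the planned size.** Pooled SD = √((25 + 36)/2) = 5.52. With (1.960 + 0.842)² = 7.849, n per arm = 2 × 30.5 × 7.849 / 36 = 13.3. Dividing by 0.9 gives 14.8, rounded up to 15, so 30 in total. The protocol's figure reproduces.

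**Step 2: precision of an SD from six patients.** The 95% limits are the estimate times √(5/χ²) at the 97.5% and 2.5% points of chi-square with 5 df, which gives 0.62 to 2.45 times the estimate. Because n is proportional to SD², the size is far less certain than the SD.

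**Step 3: carry this through the formula.** Draw s² = SD² × χ²₅/5 (400,000 draws), set n = ⌈2 s² × 7.849 / 36 / 0.9⌉ with a minimum of 2, and take the noncentral-t power at that n for a true difference of 6, all patients evaluable. With the planned SDs true:

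- n per arm: median 13, 95% range 3 to 38; below 15 in 55% of draws, at most 10 in 36%
- power: mean 71%, below 60% in 31% of draws, below 50% in 20%
- for comparison, a fixed 15 per arm gives 82%

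The rounding convention matters a little. Rounding before the allowance for losses, and counting power on evaluable patients, gives 52% below 15 and mean power 68%, against 79% at a fixed 14 evaluable. A t-based recalculation gives 47% and 72%. Hence about an even chance, and mean power of about 70%.

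**Step 4: vary the true SD** (same rule as step 3).

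| True SD | Chance n < 15 per arm | Mean power, recalculated | Power, fixed 15 per arm |
|---|---|---|---|
| 5 and 6 | 55% | 71% | 82% |
| 6 | 45% | 72% | 75% |
| 7.5 | 23% | 72% | 56% |
| 10 | 8% | 73% | 35% |
| 20 | 0.4% | 73% | 12% |

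**Step 5: add a floor.** With the planned SDs true and n not allowed below 15 per arm, mean power rises from 71% to about 86%.

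**Step 6: the printed totals.** Gastrointestinal: 30 + 6 = 36, which agrees. Haematologic: 28 newly diagnosed + 6 relapsed + 6 phase I = 40, against 46 printed. Neither total can come from phase I data.

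**The case against.** The strongest reply is that the simulated rule is not in the document. The article names no parameter, formula or direction, and a condensed article may leave these to the full protocol. It also states the aim as an adequate size, and amendments go to the ethics committee and the regulator. All of this is fair, and the absence of a formula or floor is not in itself the finding. It does not rescue the step, because the weakness lies in the data source, which the article does fix: six patients, no comparator, a changed dose and no scheduled efficacy measure.

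A reader might infer that the recalculation would more often than not shrink the trial. The documents do not support that. It is near a coin toss only if SDs of 5 and 6 are right, and step 4 shows the chance falling quickly as the SD grows. If effect and SD were both re-estimated and the six patients truly showed half the planned effect, the gastrointestinal size would fall below plan in 17% of cases and would usually grow. The loss of power under an SD-only rule comes from the noise in the estimate.

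No comparable figure can be given for leukaemia. The documents state no control remission rate, so any worked example would rest on an invented one. Nor does it follow that leukaemia should be fixed at 28: whether that figure is sound is a separate question.

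The last objection also stands in part. Forbidding all reassessment would leave a fixed 15 per arm with 56% power at an SD of 7.5 and 35% at 10. And the Discussion leaves the evaluation of efficacy to phase III, which limits the weight of the point.

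**Conclusion.** The point holds in this form. The article commits the sponsor to resizing phase II from a phase I that cannot inform efficacy, and it presents totals as recalculated before phase I has started. This follows from the text alone and needs no simulation.

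The numerical size is conditional. It assumes an SD-only update without a lower limit, six patients per tumour type and a two-sided test. On those terms, with the planned SDs true, the gastrointestinal size runs from 3 to 38 per arm, with about an even chance of being below 15 and mean power about 70% against the stated 80%. With larger SDs shrinkage is less common, but mean power stays near 72%. The change should be made. It is cheap, and it protects the only randomised comparison.

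**What to change.** In Sample size {14} and Interim analyses {21b}, state that phase I data inform safety only and may not reduce the phase II sizes below those planned, which is 15 per arm for the gastrointestinal part. Present 36 and 46 as planned totals, remove the word *recalculated*, and reconcile each total with its components, in particular 46 against 28 + 6 + 6 = 40.

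This costs wording only and adds nobody beyond the planned 30 gastrointestinal patients. The sponsor gives up the option of shrinking phase II on phase I data.

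Optional: to guard against an SD larger than planned, base a reassessment on the blinded pooled QLQ-C30 SD during phase II, with the same floor of 15 per arm. Its downside is that it may add patients, so the sponsor should decide whether it can carry that.

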### Recruitment {15}

The recruitment of patients will start in July 2023 and conclude by February 2023 at the Centro Javeriano de Oncologia of the Hospital Universitario San Ignacio. As a renowned cancer treatment center in Colombia, the San Ignacio University Hospital offers comprehensive oncology programs, enabling all clinical staff involved in the study to identify and track potential candidates. Preselected patients will be contacted and provided with a detailed explanation of the study, along with the informed consent form. Subsequently, an enrollment visit will be conducted to ascertain the patient's decision regarding participation. Once enrolled, each patient will be assigned a dedicated coordinator responsible for organizing visits and follow-ups, ensuring the seamless execution of study activities. Patients will be informed of their right to withdraw from the study at any time without compromising their ongoing clinical treatment.

## Assignment of interventions: allocation

### Sequence generation {16a}

During the screening visit, all participants will be assigned a unique subject number in sequential order (e.g., 001, 002, 003, etc.), which will remain consistent throughout the study. The treatment chosen by the attending physician will be administered to all participants, without randomization in phase I.

In phase II, patients with gastrointestinal tumors will undergo randomization using a specially designed application within the eCRF in RedCap®. The randomization will be conducted using a simple non-stratified approach, predetermined, and loaded into the eCRF for the pharmacist, who will be unblinded. Randomization will not be employed for acute leukemias, as the comparison of outcomes will be conducted against a historical group using propensity score matching.

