### Eligibility criteria {10}

#### Inclusion criteria

##### Gastrointestinal tumors:

Patients aged 18 years or older, with no upper age limit.Histological diagnosis of gastrointestinal cancer, including stomach, colon, bile ducts, and pancreas.Measurable disease confirmed by diagnostic tests and planned to receive chemotherapy as the primary treatment.Presence of at least one discrete metastatic site identified by CT scan of the chest and/or abdomen and/or bone scintigraphy.ECOG performance status of 0 to 2, with a life expectancy greater than 2 months.Ability to swallow and retain oral medication, and absence of uncontrolled emesis or persistent diarrhea.Adequate renal, hepatic, and cardiac function defined as follows:Renal Function: Glomerular filtration rates greater than 30 mL/min, determined by blood chemistry (CKD-EPI calculation) and/or urinary creatinine clearance and/or Glomerular filtration scintigraphy.Liver Function: Alkaline phosphatase, ALT, and AST should not exceed 5 times the reference value according to laboratory technique. Bilirubin should not exceed 3 times the reference value.Cardiac Function: Echocardiogram and/or electrocardiogram results should indicate no untreated or decompensated heart failure, with an ejection fraction greater than or equal to 50%. Additionally, any value lower than the mentioned threshold, posing a risk to the patient, should be assessed by the investigator.Female patients of childbearing age who are not using safe non-hormonal contraceptive methods must undergo a negative pregnancy test prior to screening.Fertile female subjects (not postmenopausal for at least 12 months or surgically sterile) and their male partners must use one of the following contraceptive methods from study entry, throughout the study, and for at least 6 months after using Esperanza extract (unknown effects on the developing fetus):Complete abstinence from sexual intercourse, beginning at least one complete menstrual cycle before study drug administration (note: sexual abstinence as a contraceptive method should be limited to cases where it is already an established choice of the patient's pre-existing lifestyle).Vasectomy in the partner of a female subject.Intrauterine device (IUD).Double barrier method (condom, contraceptive sponge, diaphragm, or vaginal ring with spermicidal jelly or cream).Willingness to complete the study and comply with follow-up interventions.

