#### Phase II treatment:

For patients with metastatic gastrointestinal tumors (colon, pancreas, stomach, and bile ducts), a total of 30 new patients will be enrolled and divided into two groups: an intervention group and a placebo group, each consisting of 15 patients. The intervention group will receive continuous treatment with the Esperanza extract at the determined maximum tolerated dose (MTD) for three treatment cycles, equivalent to approximately 12 weeks. The placebo group will receive a placebo in addition to standard chemotherapy treatment for their underlying disease. Safety evaluations will be conducted at the end of each treatment cycle, and the efficacy evaluation will be carried out after completion of the three treatment cycles. Table 2 provides a comprehensive list of the activities to be carried out during the patients' intervention.

**Table 2 Tab2:** Activity schedule for phase II clinical trial in gastrointestinal tumors

Schedule of activities					

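### Simple unstratified randomisation does not secure the stated 15 per group, and leaves avoidable chance imbalance across four tumour sites

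*Protocol article*

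**What the plan says.** - **Allocation method.** Sequence generation {16a}: "The randomization will be conducted using a simple non-stratified approach, predetermined, and loaded into the eCRF for the pharmacist". Concealment mechanism {16b} adds that the module is loaded before the study starts. Neither section mentions blocking, minimisation or any other restriction.
- **Group sizes.** Phase II treatment describes "an intervention group and a placebo group, each consisting of 15 patients". Sample size {14} agrees: "a sample size of 30 patients was calculated, with 15 patients per group".
- **Basis for the size.** Sample size {14} gives the inputs as "considering a mean difference of at least 6 points in quality of life" and "a standard deviation of 5 and 6 points for each group", with alpha 0.05, beta 0.20 and 10% for losses. That section and Interim analyses {21b} say the size will be recalculated after phase I.
- **Population.** The inclusion criteria admit "Histological diagnosis of gastrointestinal cancer, including stomach, colon, bile ducts, and pancreas", and Phase II treatment pools the same four sites. Under concomitant care {11d}, the treating oncologist chooses the chemotherapy.

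**The concern.** Two statements do not fit together. Simple randomisation in its standard sense allocates each patient independently, so group sizes are random. Yet the plan states fixed groups of 15 and sizes the trial on them. If the preloaded list is in fact restricted to 15/15, it is not simple randomisation and the text should say so.

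The second matter survives either reading. Thirty patients from four primary sites, on chemotherapy chosen patient by patient, will be split with nothing to keep the sites even. If quality of life differs by site, an uneven split moves the observed arm difference for reasons unrelated to the extract. In a trial of 30 there is little chance for this to even out, and this is the trial's only randomised comparison. A statistical analysis plan could add a covariate later, but it could not change an allocation list already in use.

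**Working it through.** **1. The plan's own figure.** Inputs from Sample size {14}: difference 6, SDs 5 and 6, alpha 0.05 (two-sided assumed, since sidedness is not stated), power 0.80.

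n per group = (1.960 + 0.842)² × (5² + 6²) / 6² = 7.849 × 61 / 36 = 13.30.

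With 10% losses, 13.30 / 0.9 = 14.8, so 15 per group and 30 in total. The stated figure is reproduced.

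**2. Group sizes under simple randomisation.** The number in one arm is Binomial(30, 0.5).

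| Split | Probability |
|---|---|
| exactly 15/15 | 14.4% |
| 12/18 or worse | 36.2% |
| 11/19 or worse | 20.0% |
| 10/20 or worse | 9.9% |

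**3. Effect on power.** Two-sample t-test, difference 6, common SD √(61/2) = 5.52, no losses: 81.9% at 15/15, 80.3% at 12/18, 77.3% at 10/20, and 80.5% averaged over all splits. The average cost is 81.9 − 80.5 = 1.4 percentage points.

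**4. Site imbalance, two groups.** The document gives no site mix. Assume 10 of 30 patients are pancreatic or biliary and score D points lower. If a of the 10 and b of the other 20 fall in one arm, so that n₁ = a + b and n₂ = 30 − n₁, the arm difference shifts by

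D × |a/n₁ − (10 − a)/n₂|.

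With both arms at 15, a 7–3 split gives D × 4/15. That is 2.67 points for D = 10 (2.67/6 = 44% of the target) and 1.33 points for D = 5 (22%). The standard error implied by the plan is √(25/15 + 36/15) = 2.02 points.

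For the simple list I summed over a ~ Binomial(10, 0.5) and b ~ Binomial(20, 0.5), letting the arm sizes vary. For the fixed list, a is hypergeometric (15 drawn from 30, of whom 10 are pancreatic or biliary).

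| Shift, D = 10 | Simple list | Fixed 15/15 list |
|---|---|---|
| at least 2.67 points | 15.8% | 24.5% |
| at least 4 points | 2.9% | 5.0% |
| at least 6 points | 0.04% | 0.02% |

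The fixed list is not really worse. Its shifts come in steps of 2/15 × 10 = 1.33 points, so 2.67 and 4 are attainable values and count in full. The spread is nearly the same: the variance of the share difference is (1/3)(2/3)(30/29)(1/n₁ + 1/n₂), so the SD of the shift is 1.75 points at 15/15 and 1.79 at 12/18.

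**5. Site imbalance, four sites.** This was simulated for assumed mixes of 8/8/7/7, 12/10/5/3, 15/8/5/2 and 20/5/3/2. The probability that the arms differ by 20 percentage points or more in the share of at least one site was 60%, 54%, 53% and 40% with a simple list, and 53–70% with a fixed 15/15 list.

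**6. With two strata and blocks of 2 and 4.** An unfinished block leaves a stratum uneven by at most 2 patients. The group of 10 therefore splits no worse than 6–4 and the group of 20 no worse than 11–9. Arm sizes stay within 13 to 17. The largest share difference is 6/15 − 4/15 = 0.133, a shift of 1.33 points for D = 10.

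**The case against.** **Simple randomisation is valid.** It is unbiased in expectation. If the planning SDs already include variation between sites, the standard error covers chance imbalance and an unadjusted test keeps its type I error. That stands, so this is a matter of avoidable imbalance and precision and not of validity.

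**Unequal arms hardly matter.** This also stands. Average power remains above 80%, and the phase II size is provisional in any case.

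**The 10-point deficit is large.** With a third of patients 10 points lower, site alone contributes variance 100 × (1/3)(2/3) = 22.2. The planned variance is 30.5, which leaves a within-site SD of √8.3 = 2.9. A 5-point deficit contributes 5.6 and leaves √24.9 = 5.0, which fits the plan better. The 10-point case is best read as an upper illustration.

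**Change scores could remove a stable deficit.** QLQ-C30 is collected at the initial visit and later. If change is compared, only site differences in course would matter. That is fair, but the statistical methods section does not fix the comparison as one of change.

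**Stronger readings that the documents do not support.**
- A reader might infer that one uneven split could produce or hide the full 6-point effect. On the assumptions above that has a probability of about 0.04%.
- A reader might take the 34% chance of a 7–3 or worse split among 10 patients and attach the 2.7-point shift to it. That combines random arm sizes with arms fixed at 15; the consistent figure is 15.8%.
- A reader might fault the absence of site covariates for progression-free survival and response. The article only summarises tests that may be used, and covariates are commonly left to the analysis plan.

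**Conclusion.** The concern holds, at moderate weight. The inconsistency between simple randomisation and fixed groups of 15 is certain on the text and needs correcting, although its cost in power is small. The substantive weakness is that nothing in the allocation limits imbalance by tumour site, and fixing the list at 15/15 would not cure that. Its size depends on two figures the document does not give: the share of pancreatic or biliary patients (one third assumed) and their quality-of-life deficit (5 to 10 points assumed). Over that range, a 7–3 split in equal arms moves the estimate by 1.3 to 2.7 points, against a target of 6 and a standard error of about 2. A shift of that size or more has a probability of roughly one in six with a simple list and one in four with a fixed list.

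**What to change.** Before phase II opens:

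1. Replace the list with permuted blocks of small, randomly varying size (for example 2 and 4), stratified by two site groups: pancreas/bile duct and stomach/colon. Load it into REDCap.
2. Amend Sequence generation {16a} to describe this. In Phase II treatment and Sample size {14}, state 1:1 allocation with approximately 15 per group, because stratified blocks do not guarantee exactly 15/15 either.
3. Adjust the primary quality-of-life comparison for the site-group stratification factor.

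The cost is a regenerated list, a short amendment and one degree of freedom in the primary model, with no added patients or visits. Blocks make some allocations slightly predictable; varying the block size and the existing double-blinding limit this. Two strata suit 30 patients better than four, which would be sparse, but balance between stomach and colon, or between pancreas and bile duct, is then still left to chance. The change cannot be made retrospectively for patients already allocated.
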